#### Composition of the data monitoring committee, its role, and reporting structure {21a}

An independent data monitoring committee (DMC) comprises members specializing in psychiatry, statistics, and ethics. DMC monitors the recruitment and follow-up of participants, the adverse effect reports, the trial outcomes, the safety and efficacy of the interventions, the quality of the CRF data, and the general conduction of the iDoT-AFD study.

#### Adverse event reporting and harms {22}

The investigators will record all the adverse events and evaluate the severity.

#### Frequency and plans for auditing trial conduct {23}

Trial audits by the representatives from the quality assurance department of SMHC are conducted every half year or any time necessary following the regulatory guidance.

#### Plans for communicating important protocol amendments to relevant parties (e.g., trial participants, ethical committees) {25}

Any protocol modification will be sent to the principal investigator (PI) to add to the investigator files. Protocol amendments will also be reported to IRB and updated in the clinical trial registry.

#### Dissemination plans {31a}

The study findings will be disseminated through presentations at the national and international scientific conferences, publications in peer-reviewed journals in psychiatry or neuroscience, evidence‑based clinical guidelines or recommendations, and textbooks on the diagnosis, treatment, and prognosis of AFD. The study data will not be shared for any purpose without the permission of the IRB and PI.

## Discussion

AFD is one of the most common clinical specifiers of MDD, closely associated with BD. The iDoT-AFD study mainly aims to find out the molecular imaging biomarkers for identifying AFD, optimize the individualized treatment for patients with AFD, and build a clinical early warning model to predict the conversion of AFD to BD. Participants are recruited from 5 clinical sites in the eastern, western, southern, northern, and central regions of China to assure a broadly representative population. Accordingly, the findings of the iDoT-AFD study would be also widely characteristic and generalizable. The iDoT-AFD study is a multicenter, prospective, randomized study, which can provide evidence for clinical guidelines for the diagnosis, treatment, and prognosis of AFD.

### Limitation

Except for drug-naive patients, patients with AFD who are medication-free for more than 1 week are also recruited. A washout period of 1 week is relatively short and may influence the interpretation of intervention effects. Subgroup analyses will be performed to clarify the influence, and the washout period will be more carefully determined in future studies.

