### Objectives {7}

The primary aim of the iDoT-AFD study is to identify the molecular imaging biomarkers for AFD by analysis of KP metabonomics and multimodal magnetic resonance imaging (MRI). The secondary aim of the iDoT-AFD study is to find out the optimized intervention and the predictive biomarkers of treatment effectiveness in patients with AFD. The third aim of the iDoT-AFD study is to screen out the risk factors and build a clinical early warning model to predict the conversion of AFD to BD.

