### Eligibility criteria {10}

The inclusion criteria for patients with AFD are as follows: (1) 16–60 years old, (2) meeting the DSM-5 criteria for MDD, (3) scored 20 or higher on the Hamilton’s Depression Scale with 24 items (HAMD-24), (4) enough audiovisual ability and comprehensive ability to accomplish the interview, (5) necessary and appropriate to accept the treatment of antidepressants, (6) scored less than 14 on the Hypomania Symptom Checklist-32 (HCL-32), and (7) meeting DSM-5 specifier for atypical features: mood reactivity and 2 or more of the following—significant weight gain or increase in appetite, hypersomnia, leaden paralysis, and a long-standing pattern of interpersonal rejection sensitivity that results in significant social or occupational impairment.

The exclusion criteria for patients with AFD are as follows: (1) severe medical or neurological problems; (2) previous episodes of mania or hypomania; (3) female patients who are pregnant, planning to be pregnant, or breastfeeding; (4) high risk of suicide; (5) had ECT, MECT, or rTMS in the past 6 months; and (6) experienced severe personality disorder, mental retardation, and anorexia/bulimia nervosa.

Additionally, all included patients with AFD should be drug-naive or medication free for more than 1 week.

The inclusion criteria for patients with BD are as follows: (1) 16–60 years old, (2) meeting the DSM-5 criteria for major depressive episode of bipolar I disorder or bipolar II disorder, (3) scored 20 or higher on the HAMD-24, and (4) enough audiovisual ability and comprehensive ability to accomplish the interview.

The exclusion criteria for patients with BD are as follows: (1) severe medical or neurological problems; (2) female patients who are pregnant, planning to be pregnant, or breastfeeding; (3) high risk of suicide; (4) had electroconvulsive therapy, modified electroconvulsive therapy, or repetitive transcranial magnetic stimulation in the past 6 months; and (5) experienced severe personality disorder, mental retardation, and anorexia/bulimia nervosa.

The inclusion and exclusion criteria for HC are as follows: (1) 16–60 years old, (2) enough audiovisual ability and comprehensive ability to accomplish the interview, and (3) no history of mental disorder or serious somatic disease.

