### Data collection and management

#### Plans for assessment and collection of outcomes {18a}

M.I.N.I International Neuropsychiatric Interview (MINI) [19] is used to conduct a comprehensive screening. HAMD-24 and Quick Inventory of Depressive Symptomatology (self-report) with 16 items (QIDS-SR16) [20] are applied to evaluate depressive symptoms, Hamilton’s Anxiety Scale (HAMA) [21] is used to assess anxious symptoms, HCL-32 is performed to recognize mania or hypomania symptoms, and Quality of Life Scale with 6 items (QOL-6) [22] is used to evaluate the life quality briefly. Additionally, family history, physical or mental comorbidity, the medication used before, prescription for this time, number of episodes, first-onset time and age, and duration of illness are also questioned and recorded. Adverse events are recorded in adverse events report (AER) forms when needed during the follow-up period. Cognitive function is assessed using the MATRICS Consensus Cognitive Battery (MCCB) [23]. MCCB consists of 10 subtests that mainly reflect the cognitive function of 7 cognitive domains including speed of processing, attention and vigilance, working memory, verbal learning, visual learning, reasoning and problem-solving, and social cognition.

After the 12-week randomized intervention, patients with AFD will be followed up until switching to BD for a maximum of 4 years. Face-to-face interviews, including clinical and neurocognitive assessments, MRI scans, and blood specimen collection, will be scheduled for 12 weeks, 1 year, and 4 years. The interim interviews of clinical assessments will be performed at 2 weeks, 4 weeks, 8 weeks, 6 months, 2 years, and 3 years through offline or online approaches. Patients with AFD will undergo a semi-structured interview at the follow-up time points to determine whether they have experienced mania or hypomania or have been diagnosed with bipolar disorder by psychiatrists during the interval since the previous follow-up. If a patient has experienced mania or hypomania or has been diagnosed with bipolar disorder by psychiatrists during the interval, multidimensional data will be recollected and follow-up will be terminated.

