### Methods for additional analyses (e.g., subgroup analyses) {20b}

To explore the potential biomarker identifying AFD, analysis of variance (ANOVA), Kruskal–Wallis tests, or chi-square tests will be applied to compare the group differences of multivariate-dimension information among the first-episode AFD patients, recurrent AFD patients, and patients with BD and HC.

The prediction model of patients with AFD switching from depression to mania or hypomania will be constructed. Multidimensional data obtained at baseline and their changes during the follow-up period will be used to predict the binary outcome (switching to mania/hypomania or not). The concordance index will be calculated to assess the discrimination of the model. Construction of the multivariate prediction model will be conducted by collaborators specializing in biomedical engineering.

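### The planned remedy for the one-week washout covers only the randomised comparison and leaves the unadjusted biomarker comparison at risk of confounding by recent medication

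*Protocol article*

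**What the plan says.** - **Entry (Eligibility criteria {10}).** The AFD group mixes two kinds of patient: "all included patients with AFD should be drug-naive or medication free for more than 1 week". No medication condition is stated for the BD group.
- **Acknowledged weakness (Limitation).** "A washout period of 1 week is relatively short and may influence the interpretation of intervention effects". The response is "Subgroup analyses will be performed to clarify the influence". Neither the subgroup factor nor the outcome is named, but the influence meant is the one on intervention effects in the preceding sentence.
- **Biomarker comparison (Methods for additional analyses {20b}).** The tests are fixed as plain group tests: "analysis of variance (ANOVA), Kruskal–Wallis tests, or chi-square tests will be applied to compare the group differences of multivariate-dimension information". Four groups are set against each other in this way: AFD split by episode history, BD, and healthy controls. No medication stratum or covariate is mentioned.
- **Rank of that comparison (Objectives {7}).** "The primary aim of the iDoT-AFD study is to identify the molecular imaging biomarkers for AFD".
- **Covariates (Statistical methods {20a}).** The only covariates given are demographic factors and initial depression severity. They belong to the repeated-measures model of HAMD scores in the trial, and prior medication is not among them.
- **Data available (Plans for assessment and collection of outcomes {18a}).** The items recorded include "the medication used before, prescription for this time, number of episodes".

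**The concern.** The article recognises that recent medication may disturb interpretation, then applies its remedy to the better protected of two analyses. Allocation to the four arms is random within site, so drug-naive and washed-out patients should be spread evenly over the arms apart from chance. Nothing does the same for first-episode and recurrent patients. A recurrent patient has had at least one earlier episode and therefore more opportunity to have been treated. If recent medication is more common among recurrent patients and leaves some trace in kynurenine-pathway metabolites, functional MRI or cognition, an unadjusted test will attribute that trace to episode status.

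At stake is the comparison that serves the study's first-ranked aim. A marker could appear to separate the AFD subgroups when part or all of the difference reflects drugs stopped shortly before sampling.

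**Working it through.** **The plan's own figure.** The article has no calculation for the biomarker comparison. Its only sample-size calculation is for the trial, and it reproduces: n = 2 × (1.960 + 0.842)² / 0.5² = 62.8, so 63 per group, and 63 / 0.70 = 90 after drop-out. The point here does not depend on it.

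**The two analyses side by side.**

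| | Treatment comparison | Biomarker comparison |
|---|---|---|
| Groups formed by | randomisation, stratified by site | diagnosis and episode history |
| Prior medication balanced? | yes, in expectation | no mechanism |
| Covariates stated | yes (not medication) | none |
| Washout named as a threat? | yes | no |
| Remedy stated | subgroup analyses | none |

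**Size of the possible bias.** Only the total of 480 AFD patients comes from the article. Everything else is assumed:
- split of first-episode to recurrent patients between 30:70 and 70:30;
- share recently medicated higher in recurrent patients by Δp = 0.20 to 0.60;
- residual drug effect δ = 0.2 to 0.5 SD on a marker;
- no true difference between first-episode and recurrent patients.

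Formulas:
- bias b = Δp × δ;
- SE = √(1/n₁ + 1/n₂), in SD units;
- false-positive rate = 1 − Φ(1.96 − b/SE) + Φ(−1.96 − b/SE).

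Standard errors:
- Even split, 240 and 240: SE = √(2/240) = 0.0913.
- 30:70 split, 144 and 336: SE = √(1/144 + 1/336) = 0.0996.

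| Split | Δp | δ (SD) | b (SD) | b/SE | False-positive rate |
|---|---|---|---|---|---|
| any | 0 | any | 0 | 0 | 5% |
| 30:70 | 0.20 | 0.2 | 0.04 | 0.40 | 7% |
| 50:50 | 0.40 | 0.2 | 0.08 | 0.88 | 14% |
| 50:50 | 0.40 | 0.3 | 0.12 | 1.31 | 26% |
| 50:50 | 0.60 | 0.3 | 0.18 | 1.97 | 50% |
| 50:50 | 0.60 | 0.5 | 0.30 | 3.29 | 91% |

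**Fewer patients with imaging.** Neuroimaging assessments are made at available sites, so imaging numbers may fall below 480. With an illustrative 120 per group, SE = √(2/120) = 0.129. A bias of 0.18 SD then gives b/SE = 1.39 and a rate of about 29% instead of 50%. The bias itself is unchanged; only the chance of declaring it significant falls.

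This is a two-group approximation for one contrast and one marker, whereas the article describes a four-group comparison. Contrasts with the BD group may also be exposed, since no medication condition is stated for it; they are not quantified here.

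**The case against.** The strongest reply is that this is a condensed article about a study that calls itself exploratory. Covariates and sensitivity sets for biomarker tests are often left to the full protocol or analysis plan. The section lists families of tests and does not say that medication will be ignored, and the Limitation section does not expressly exclude biomarker subgroups. This has weight: an unseen plan may already adjust. But the point rests on what the article states, namely a recognised weakness, a scope for it, a remedy tied to that scope, and unadjusted tests for the comparison outside it. That scope is too narrow as written.

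Some stronger readings are tempting but not supported:

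- **That episode status and recent medication are almost the same variable.** The article gives no medication shares. A first-episode patient may have been treated in the current episode, and a recurrent patient may never have been treated. If the two variables nearly coincided, adjustment could hardly separate them. Only a risk of confounding, of unknown size, is supported.
- **That a false marker of recurrence would be reported.** The stated aim is markers of AFD; a recurrence marker is not an objective. The contrast is nevertheless among those the article plans to make.
- **That recently stopped drugs helped some patients meet the atypical-features criterion.** Nothing in the article bears on this, and how symptoms count towards the diagnosis is a clinical matter outside this point.
- **That the rate is 91%, or any other single figure.** Every input except the 480 is assumed.

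**Conclusion.** The concern holds in limited form. The article treats the short washout as a problem only for intervention effects, where randomisation already gives protection in expectation. It plans no allowance for recent medication in the non-randomised biomarker comparison that serves its primary aim. That comparison is at risk of confounding.

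The size cannot be determined from the article. Over the assumed ranges, the spurious first-episode versus recurrent difference is 0.04 to 0.30 SD and the false-positive rate about 7% to 91% with all 480 AFD patients. The rate is lower where fewer patients have imaging, and both the bias and the excess error vanish if medication shares are equal or drugs leave no residual effect. The length of the washout is a clinical matter and is not judged here.

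**What to change.** Extend the medication-status analysis promised under Limitation to the biomarker comparison under Methods for additional analyses {20b}:

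1. Use a regression or ANCOVA form of the AFD biomarker comparison, with the first-episode versus recurrent contrast adjusted for drug-naive versus washed-out status. Add time since last dose only if it was recorded; the article mentions prior medication but not stop dates.
2. Repeat the AFD biomarker comparisons in drug-naive patients as a sensitivity analysis, and report it alongside the main result.
3. Tabulate drug-naive and washed-out numbers by episode status, so that readers can see how far the two overlap.

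The cost is wording plus one derived variable from data already collected; no new visits or samples are needed. The price is precision: the adjusted contrast will be less precise the more the two variables overlap, and the drug-naive analysis may be weak if few recurrent patients are drug-naive.

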## Trial status

This paper is based on the study protocol version 03 of October 19, 2019. The iDoT-AFD study was registered in ClinicalTrials.gov using ID NCT04209166 on December 19, 2019. The first enrollment of participants was on August 13, 2019; the recruitment is planned to be completed before October 2022; and the follow-up will be continued until 4 years later or all participants reach the study endpoint.

## Data Availability

The datasets analyzed during the current study and statistical code are available from the corresponding author upon reasonable request, as is the full protocol.

## Abbreviations

iDoT-AFD: Individualized Diagnosis and Treatment for Depression with Atypical Features
AFD: Depression with atypical features
MDD: Major depressive disorder
BD: Bipolar disorder
HC: Healthy control
RCT: Randomized controlled trial
DSM-5: Diagnostic and Statistical Manual of Mental Disorders, Fifth Edition
BIPAS: National Bipolar Mania Pathway Survey
KP: Kynurenine pathway
EDTA: Ethylene diamine tetraacetic acid
MRI: Magnetic resonance imaging
SMHC: Shanghai Mental Health Centre
PI: Principal investigator
CTC: Clinical trial coordinator
HAMD-24: Hamilton’s Depression Scale with 24 items
HCL-32: Hypomania Symptom Checklist-32
SSRI: Selective serotonin reuptake inhibitor
SNRI: Serotonin-noradrenaline reuptake inhibitor
TAU: Treatment as usual
MINI: M.I.N.I International Neuropsychiatric Interview
QIDS-SR16: Quick Inventory of Depressive Symptomatology (self-report) with 16 items
HAMA: Hamilton’s Anxiety Scale
QOL-6: Quality of Life Scale with 6 items
MCCB: MATRICS Consensus Cognitive Battery
DTI: Diffusion tensor imaging
DKI: Diffusion kurtosis imaging
ANOVA: Analysis of variance
DMC: Data monitoring committee
eCRF: Electronic case report form
